### Provisions for post-trial care {30}

Once the intervention completed, the mobile app for the intervention group will be deactivated, and they will be returned to standard diabetes care. In case of injury, care will be provided at HMC without cost, but any outside care will be at the participant’s expense.

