#### Secondary outcomes

Secondary outcomes include differences in:Perceptions of diabetes self-management as assessed by diabetes self-management questionnaire (DSM-Q) [24]; a self-completed questionnaire including 16 items assessing selfcare activities associated with glycaemic control at 0 and 6 months;Attitudes towards disease assessed using the diabetes distress scale (DDS) [25]; a 17-item participant-completed questionnaire assessing psychosocial distress in diabetes at 0 and 6 months;Number of recommended insulin dose adjustments;Number of reported hypoglycaemic events;The time required to reach normoglycaemia;The number of clinical interactions;The proportion of missed clinical appointment;In anthropometric measures (body weight; body mass index [BMI]), blood pressure and lipid profile;Key outcome measures beyond 6 months with follow-up (up to 5 years).

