**Fig. 3 Fig3:**
[figure not shown]
Flow of participants

Expected duration: the intervention will be for 6 months with further follow-up to examine distal clinical outcomes of interest. Participants consent to follow-up of up to 5 years.

Participants must complete at least visit 0 and 6 months to be considered as study completers.

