## Statistical methods

### Statistical methods for primary and secondary outcomes {20a}

Descriptive statistics will be used to summarise and determine the sample characteristics and distribution of patients’ data. The normally distributed data and results will be reported with mean and standard deviation (SD) with corresponding 95% confidence interval (CI); the remaining results will be reported with median and inter-quartile range (IQR). Categorical data will be summarised using frequencies and proportions. Associations between two or more qualitative data variables will be assessed using chi-square (*χ*^2^) test or Fisher exact test, as appropriate. Quantitative data between the two independent groups will be analysed using unpaired *t* or Mann-Whitney *U* test as appropriate.

The analysis will follow the intention to treat principle with last observation carried forward. Difference in mean change from baseline HBA1c between the intervention arm and the standard care arm at 3 and 6 months will be analysed using repeated measure ANOVA method, linear regression and analysis of covariance (ANCOVA) methods as appropriate. Sensitivity analysis will be conducted using other approaches based on data available. Comparisons will be conducted between trial group and the observational cohort using the approaches described above.

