## Discussion

QDMAT is the first randomised clinical trial in Qatar aiming to test whether the use of a mobile app to support medical and self-management of insulin-treated T2DM results in improved glycaemic outcomes. Little is known about conducting clinical trials of mHealth interventions in Qatar, and the progress of the trial will inform future similar interventions. Anticipated challenges to the trial conduct include subject recruitment and retention. While the population of Qatar report willingness to participate in clinical studies and those who have participated in previous studies report a positive experience, there are several barriers to study participation [21]. These barriers are common to studies outside Qatar and include time commitment for study participation and lack of awareness of clinical research. This may not be a barrier in QDMAT since the use of the mobile app allows participants to manage diabetes remotely. Also, all assessments are conducted simultaneously with planned clinical visits. Furthermore, the population with diabetes in Qatar are younger than western populations and use technology frequently for health purposes [17, 18]. Recruitment into clinical research studies has benefitted greatly from the introduction of electronic medical records across Qatar (in both primary and secondary care) and diabetes registries. This allows rapid identification of patients for targeted clinical care as well as for research participation [27]. Qatar has a diverse population including a large expatriate population which can affect participant retention and long-term follow-up. Longer residence in Qatar is associated with greater willingness to enrol in clinical research and greater probability of participant retention [21]. The 6-month duration of QDMAT should ensure that the majority of study participants remain within the country.

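### Last observation carried forward is stated without a time limit, so values measured on the app could be carried into the off-app follow-up and make a fading effect look partly lasting

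*Protocol article*

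**What the plan says.** Four parts of the protocol article bear on this point.

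- **Secondary outcomes.** A single list, opened by "Secondary outcomes include differences in", holds the measures taken during app use and, as its last item, "Key outcome measures beyond 6 months with follow-up (up to 5 years".
- **Participant timeline {13}.** The text under Figure 3 says that "the intervention will be for 6 months with further follow-up to examine distal clinical outcomes of interest", and that "Participants consent to follow-up of up to 5 years".
- **Provisions for post-trial care {30}.** At the end of the intervention, "the mobile app for the intervention group will be deactivated, and they will be returned to standard diabetes care".
- **Statistical methods for primary and secondary outcomes {20a}.** "The analysis will follow the intention to treat principle with last observation carried forward". No time limit is attached. The next sentence names 3 and 6 months for the HbA1c comparison and lists candidate models. The section on non-adherence and missing data {20c} repeats intention to treat only. No separate rule is given for the period after month 6.

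On later retention, the Discussion says: "Qatar has a diverse population including a large expatriate population which can affect participant retention and long-term follow-up". It gives no figure.

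**The concern.** Carrying a value forward treats it as a stand-in for the missing later value. Here the treatment changes at month 6. A value recorded at month 6 or earlier in the intervention arm was measured with the app in use; the value it would replace belongs to a time when the app is off. If the app's effect fades after deactivation, the carried values keep part of the 6-month difference alive in the later comparison.

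This does not need unequal dropout. With the same loss in both arms, and loss unrelated to outcome, the 6-month difference is still copied into later time points in proportion to the share carried. When the effect fades, the error favours persistence. At stake is a claim of lasting benefit that comes from the missing-data rule and not from later measurements.

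**Working it through.** **The plan's own figure.** Inputs from Sample size {14}: difference 0.5%, revised SD 1.7%, 80% power, significance level 0.05 (taken as two-sided, since sidedness is not stated).

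- n per arm = 2 × (1.960 + 0.842)² × 1.7² / 0.5² = 181.5, rounded up to 182, as stated.
- With 40% dropout: 182 / 0.6 = 303.3, rounded up to 304 per arm, 608 in total, as stated.

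**Assumptions for the illustration.**

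- Effect at 6 months: 0.5%, the difference the protocol plans for. True effect after deactivation: 0.
- 304 per arm and SD 1.7%, as above, with the same SD used for late values.
- 60% seen at 6 months, from the planned 40% dropout.
- Early dropouts carry no app effect.
- A share g of those seen at 6 months has no later value. The documents give no figure for g, so a range is shown.

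**Formulas.**

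- False late difference: b = 0.5 × 0.6 × g
- SE = 1.7 × √(2/304) = 0.138
- Probability of declaring a difference: Φ(b/SE − 1.96) + Φ(−b/SE − 1.96)

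| g | b (% HbA1c) | b/SE | Probability |
|---|---|---|---|
| 0 | 0 | 0 | 5% |
| 25% | 0.075 | 0.54 | 8.5% |
| 50% | 0.150 | 1.09 | 19% |
| 75% | 0.225 | 1.63 | 37% |

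**How far the assumptions matter.**

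- *Early dropouts carry half the effect (0.25%).* Then b = 0.4 × 0.25 + 0.6 × g × 0.5. For g from 20% to 80%, b is 0.16% to 0.34% and the probability 21% to 69%.
- *Only the overall carried share f matters, all at the full 0.5%.* Then b = 0.5 × f. For f = 20%, 40%, 60% and 80%, b is 0.10%, 0.20%, 0.30% and 0.40%, and the probability 11%, 31%, 59% and 83%. A simulation at f = 40%, with correlation 0.6 between the two time points, gave 0.20% and 30%.
- *Nothing is carried past month 6 and missingness is unrelated to outcome.* A vanished effect is estimated as 0 and the rate stays at 5%.

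**The case against.** A reader might infer that the long-term outcome is itself invalid, because it compares past users with never-users under an objective about using the app. The documents do not support that. The participant timeline separates the 6-month intervention from later follow-up, the post-trial care section states the deactivation openly, and no section claims that the late comparison estimates continued use. Whether the offer of 6 months of the app leaves a lasting effect is a valid randomised question, and the objective on glycaemic control is served by the 6-month primary outcome.

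A reader might also infer that the protocol deliberately prescribes carrying values to year 5. That is too strong as well. The HbA1c sentence names only 3 and 6 months, sensitivity analyses by other approaches are foreseen, and the authors may never have meant the rule for later data. The article is condensed, and long-term methods may be set out elsewhere. What remains is that the rule is stated generally, under a heading that covers secondary outcomes, with no limit and no alternative for the late period. That is a stated rule with too wide a scope, and not merely a missing detail.

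The size is open to challenge too. The Discussion says only that long-term follow-up can be affected; it does not predict heavy loss. The data collection section {18a} says that most data come from electronic medical records, which may supply later values for participants who stay in care. The main illustration also assumes a full 0.5% effect followed by none, and even then the false difference is less than half of the 0.5% that the protocol calls clinically relevant. These limits stand, and they are why the figures are an illustration and not a forecast.

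**Conclusion.** The point holds for the missing-data rule and not for the choice of outcome. Applied as written, the rule would carry on-app values into the off-app period for anyone without later data, so an effect that fades would appear partly to persist. Under the main assumptions, the false late difference is about 0.08% to 0.23% HbA1c, with a false-positive rate of about 9% to 37% in place of 5%. It could be larger if early dropouts also carry an effect, and it is small if late follow-up is nearly complete. The direction depends on the effect fading; the size depends on late missingness, which the protocol does not state. The 6-month primary result is not affected by this point.

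**What to change.** In the statistical methods section {20a}:

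- State that no value from month 6 or earlier is carried past month 6.
- Analyse outcomes beyond 6 months by randomised arm, from measurements made after deactivation, with a likelihood-based repeated-measures model or multiple imputation under a stated missing-data assumption. Simply comparing those with observed late values would not be enough, because participants who leave the country may differ from those who stay.
- Describe the comparison as the persisting effect of having been offered 6 months of app use.

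The outcome can stay in the secondary list. The change is one of wording and analysis specification and needs no change to treatment or visits. Its price is a less precise and possibly less favourable long-term estimate, which depends on the missing-data assumption.

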#### Exploratory outcomes and additional analyses

Exploratory outcomes and additional analyses include:Further analysis of patient characteristics in terms of responders and non-responders to the mobile intervention;Reduction in hospital admissions;Comparison of groups to the observational cohort will be made.

Adverse events: adverse events will be recorded throughout the trial.

### Participant timeline {13}

Table 1 shows the schedule of visits and assessments, and Fig. 3 shows the flow of participants.

**Table 1 Tab1:**
[figure not shown]
Schedule of enrolment, intervention, study visits and assessments for both study groups

*SUS* System Usability Scale, *BP* blood pressure, *HR* heart rate, *DSM-Q* Diabetes Self-Management Questionnaire, *DDS* Diabetes Distress Scale

**Fig. 3 Fig3:**
[figure not shown]
Flow of participants

Expected duration: the intervention will be for 6 months with further follow-up to examine distal clinical outcomes of interest. Participants consent to follow-up of up to 5 years.

Participants must complete at least visit 0 and 6 months to be considered as study completers.

### Sample size {14}

The initial sample size was based on a clinically relevant difference in HbA1c of 0.5% (5.5 mmol/mol) with SD 1% (11 mmol/mol) between the intervention and the standard care arms [26]. To achieve an 80% power and a significance level of < 0.05, 64 participants would be required in each arm. Assuming a 40% loss to follow-up, 90 participants were planned to be recruited in each arm. However, review of baseline characteristics of recruited participants by the trial steering group identified a higher SD of 1.7% (19 mmol/mol) giving 182 participants per arm, with a total recruitment of 608 participants to include a 40% dropout. Therefore, it was decided to extend recruitment beyond the initially planned number to 608 participants. Sample size calculations were made using STATA 15 MP. For the population cohort comparator group, we aim to select a sample 200 patients identified through the available diabetes registries to examine the impact of trial arms compared to a non-randomised group.

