**Methods:**

The planned study is an ongoing open-label randomised controlled trial in which adults living with T2DM treated with insulin will be randomised 1:1 to the use of this diabetes application versus current standard care. The primary outcome will be the difference in mean HbA1c from baseline to 6 months. Other outcome measures include anthropometric measures, hypoglycaemic events, medication adjustments, number of clinical interactions and missed appointments and patient perceptions of their disease and diabetes self-management. The study will randomise 180 subjects for assessment of the primary outcome.

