### Trial design {8}

QDMAT is an ongoing open-label parallel group randomised clinical trial. Participants with T2DM who are treated with insulin will be randomised with a 1:1 ratio into an intervention arm and standard care arm. Participants in the intervention arm will receive care through the Droobi mobile app in addition to their standard care. Participants in the control group will receive the usual DM care based on national and international DM care guidelines [22, 23].

A diabetes population comparator group will be used to examine the natural progression of diabetes and its treatment outside the randomised controlled trial. This population will contextualise and determine the effectiveness of the trial arms compared to a non-randomised population.

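### The initial 90 per arm allows for about 29% loss, not the stated 40%; the revised 608 is inflated correctly, but the abstract still gives the superseded 180

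*Protocol article*

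**What the plan says.** The sample size section (Protocol article, item 14) works in two stages. The first takes a difference in HbA1c of 0.5% and an SD of 1%, and concludes: "To achieve an 80% power and a significance level of < 0.05, 64 participants would be required in each arm". The allowance for attrition follows: "Assuming a 40% loss to follow-up, 90 participants were planned to be recruited in each arm".

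The second stage comes after the steering group saw a baseline SD of 1.7% among recruited participants. The article describes this as "giving 182 participants per arm, with a total recruitment of 608 participants to include a 40% dropout", and reports that "it was decided to extend recruitment beyond the initially planned number to 608 participants".

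The Methods paragraph of the abstract gives a different total: "The study will randomise 180 subjects for assessment of the primary outcome". With the 1:1 allocation stated under Trial design, 180 is twice the initial 90.

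**The concern.** An allowance for 40% loss should leave the required number of evaluable participants once 40% have gone. Ninety per arm does not: 60% of 90 is 54, ten short of the 64 that the preceding sentence requires. The revised figure in the same paragraph does meet this test, so the paragraph uses two different rules for the same 40%.

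Two things are at stake. First, the initial size does not deliver the power it was built to deliver, and double that size is the number a reader of the abstract takes away. Second, the increase during the trial is introduced through the larger SD. The change of inflation rule also contributed to it, and the article does not mention that change.

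**Working it through.** **Inputs (all from the sample size section unless noted).** Difference 0.5%; initial SD 1%; revised SD 1.7%; power 80%; significance level 0.05; loss 40%; allocation 1:1 (Trial design). Sidedness is not stated. Two-sided is assumed because it reproduces the stated 64; a one-sided test needs only 50 per arm.

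**1. Evaluable number, initial stage.** A two-sample t-test with standardised difference 0.5/1 = 0.5, two-sided 0.05 and 80% power needs 63.8, so 64 per arm. The stated 64 reproduces, with power 80.1%.

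**2. Inflation, initial stage.**
- n × (1 + 0.40): 64 × 1.4 = 89.6, so 90. This is the stated figure.
- n / (1 − 0.40): 64 / 0.6 = 106.7, so 107 per arm, or 214 in total.
- Shortfall: 107 − 90 = 17 per arm, or 34 in total.

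**3. What 90 per arm delivers.**
- Evaluable after 40% loss: 90 × 0.6 = 54 per arm.
- Power at SD 1%, normal approximation: Φ(0.5 / (1 × √(2/54)) − 1.96) = Φ(2.598 − 1.960) = 73.8%. The t-test gives 73.1%.
- Largest loss that still leaves 64: 1 − 64/90 = 28.9%.

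**4. Inflation, revised stage.**
- Evaluable at SD 1.7%: the normal approximation gives 182 per arm, as stated. The t-test gives 182.4, an immaterial difference.
- 182 / 0.6 = 303.3, so 304 per arm and 608 in total. The stated 608 reproduces with division by 0.6.
- The 1.4 rule would have given 182 × 1.4 = 254.8, so 255 per arm and 510 in total.

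**5. Splitting the rise from 180 to 608.** The total rise is 608 − 180 = 428.
- Change the SD first and keep the 1.4 rule: 180 to 510, a rise of 330. Then change the rule: 510 to 608, a rise of 98 (98/428 = 23%).
- In the other order, correcting the rule adds 34 (180 to 214) and the SD adds 394 (214 to 608).

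The split depends on the order, but in both orders the SD is the main cause and the rule a real, smaller one.

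**6. The abstract's 180 at the revised SD.** With 54 evaluable per arm and SD 1.7%: Φ(0.5 / (1.7 × √(2/54)) − 1.96) = Φ(1.528 − 1.960) = 33.3%. The t-test gives 32.8%.

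**The case against.** The strongest reply is that the figure is history. The section presents 90 per arm as the initial plan and replaces it with 608, which is correctly inflated. No current target in that section rests on 90, and the 73% describes an SD the trial has since abandoned. This stands, and it limits the consequence. A reader might infer that the trial's present target is too small because of the slip; the documents do not support that.

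A second reply is that 180 in the abstract against 608 in the body is a question of which target applies. Had the initial figure been 214, the abstract would still be out of date. This also stands. It means the relevant power for the abstract's number is the 33% at SD 1.7%, and that the abstract needs reconciling with 608 whatever is done about the inflation.

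A reader might also infer that the article attributes the increase to the SD alone. It does not say so: it gives the SD as the reason for 182 per arm and states that 608 includes the dropout allowance. What it leaves unsaid is that the allowance was computed differently the second time.

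Two further replies carry less weight. The article attaches 80% power to 64 per arm and states no power for 90 with 40% lost, so the mismatch is implied; but the only purpose of the inflation was to keep those 64. The statistical methods section plans intention to treat with last observation carried forward, under which people lost to follow-up could still enter the analysis. The sample size, however, is inflated for loss at both stages, so its own premise is that those lost do not count.

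**Conclusion.** The point holds as a wrong inflation of the initial size, with limited consequence. The stated 90 per arm reproduces only with a multiplier of 1.4. It leaves 54 per arm at 40% loss and about 73% power (74% by normal approximation), and it protects 64 per arm only up to 29% loss. The size that matches the stated premise is 107 per arm.

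The operative target of 608 is sound on its own inputs. The live residue is the abstract's 180, which conflicts with 608 and would give about 33% power at the SD the trial now assumes.

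These figures assume a two-sided 0.05 test, a comparison of two means without covariate adjustment, equal 40% loss in both arms, and no outcome information from those lost.

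**What to change.** Three changes of wording, with no effect on the 608 target, the design or the analysis:

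1. **Sample size section, initial stage.** Keep 90 per arm as the number planned, since replacing it would misreport the trial's history. Add a note that it allowed for about 29% loss, and that 40% loss would have required 107 per arm (214 in total).
2. **Sample size section, revision.** State that the rise from 180 to 608 reflects mainly the larger SD and partly the change from multiplying by 1.4 to dividing by 0.6. For scale, the 1.4 rule at SD 1.7% would have given 510, so 98 of the 428 added come from the rule when the SD is changed first.
3. **Abstract, Methods.** Change 180 to agree with the 608 in the sample size section. If the initial number is kept for context, label it as superseded.

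The cost is a few sentences in a correction or in the next protocol version.

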### Recruitment {15}

Recruitment will be from diabetes clinics at Hamad Medical corporation, pharmacy lists (insulin treatment), and diabetes registries. For the cohort observational group, identification will be via existing electronic medical records. Recruitment will also make use of approved social media announcements. Potential participants will be provided with the study information sheet prior to consent.

## Assignment of interventions: allocation

### Sequence generation {16a}

Study participants shall be randomised to one of the study arms using minimisation on age (18–40 years; 41–60 years), gender, duration of diabetes (≤ 5 years; > 5 years), and medications (oral + basal insulin; oral + basal/bolus insulin). Biphasic insulin intake was assigned to the basal/bolus group.

### Concealment mechanism {16b}

Randomisation will be done through a web-based randomisation system (www.sealedenvelope.com) accessed by study research personnel.

